#### Effect size

As the focused deterrence literature is largely based on population-level treatment effects using quasi-experimental designs and a set of outcomes (e.g. firearm homicide) that are very rare in a UK context, the study could not anticipate an effect size using the existing literature. However, other intervention types with a population at high risk for violent offending have used violence outcomes and randomised designs. The most promising intervention in the YEF Toolkit [19] is Cognitive Behavioural Therapy. CBT interventions are associated with a 25% reduction relative to controls [20]. Using this statistic as a guide, we proposed that effects of 10%, 20%, 30% and 40% relative reductions in police-recorded violence against the person would be reasonable effect sizes.

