### Outcome measures

The primary outcome for the impact evaluation is the number of violence against the person offences attributed to an individual within one year of randomisation. The secondary outcomes are:

the number of days between randomisation and a recorded violence against a person offence with a Police National Computer (PNC) disposal outcome relevant to the evaluation;when there is a co-offender, the number of recorded violence against the person offences attributed to an individual with a PNC disposal outcome relevant to the evaluation; andwhen there is a co-offender, the number of any recorded offences attributed to an individual with a PNC disposal outcome relevant to the evaluation.

For the purposes of this evaluation, PNC disposal outcomes relevant to the evaluation refer to all offences specified by the Home Office’s offence codes used in the court proceedings database as Violence Against the Person offences. Police-recorded violence against the person offences measure is the best outcome to evaluate the intervention’s effectiveness as it is a standard measure of violent behaviour [25]. Despite about half of all violent behaviour not being reported to the police, this rate decreases as the violence severity increases. Approximately 79% of violence against adults treated by a medical professional is captured, representing the most serious violent offending. However, reporting rates of violence against 10–15-year-olds are considerably lower, with less than 10% of all violence and 18% of violence resulting in medical treatment being reported [26].

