In the equation, *Y* is the outcome—in this case, a count variable measuring the number of violent offences attributed to an individual in the twelve calendar months following the randomisation of an individual. The analysis approach will be based on count outcomes. We intend to use a *zero-inflated Poisson* (as reflected in our power simulations) because many individuals will likely not have further offences in the follow-up period of 12 months post-randomisation. 1[treatment] will be a binary variable where 0 = control and 1 = treatment, and the coefficient from this variable in the model will be the focal result for the project. 2[offending frequency] is one variable used for stratification in each site. We acknowledge that there is a difference between the model used in the power calculation and the analysis model presented here (S1 File). We will update the power calculations for our statistical analysis plan once we have sample data from sites to understand the likely outcome distribution (based on pre-intervention outcome data). This will be included in the analysis as n-1 dummy categories, with the reference category being the category with the largest number of observations from low, medium, or high offending frequency (note that not pre-specifying which category now will not affect the results). 3[adult] will be a binary variable for whether an individual is an adult (over 18) (= 1) or a child (under 18 years of age) (= 0). 4[site] will be site fixed effects—dummy variables for n-1 sites, again with the site with the largest number of observations overall as the reference category (anticipated to be either Coventry or Wolverhampton in the West Midlands). We include this variable because we know, *a priori*, that sites will differ in their eligibility criteria and selection processes. Hence, we need to account for between-site variation in our analysis. Finally, 5[year/month] will be a variable that captures the year and month since the start of the delivery period. This measure will capture seasonal variation and any esoteric shocks during delivery. This will be entered as a continuous variable, but if there are model convergence problems, we will aggregate this to year-quarter. We also acknowledge that it may be necessary to include another variable for offender sex, depending on the number of females included. If necessary, this would be a binary variable with 0 = male and 1 = female, determined by sex at birth, if possible, to determine this from available data.

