### Interim analysis and ‘backfire’ check

To mitigate the risk of iatrogenic effects, interim outcome analyses will be conducted roughly six months after the trial start date, defined as the date of first randomisation in any site. These analyses will aim to identify any adverse effects and/or clear evidence of harm, given the offending seriousness of the cohort involved, focusing on the direction and magnitude of the effects. However, it will not involve statistical analysis to avoid ‘alpha spending’ [31]. In the context of this intervention, harm is defined as a negative impact on offending (averaged across sites) where the reoffending prevalence in the treatment group is equal to or more than 10 percentage points greater than the control group prevalence (e.g., 20% in treatment, 10% in control).

Likewise, to act upon the potential risk of harm, we established a set of pre-specified limits or stopping rules that will inform the decision on the study continuation post the initial six-month period. These stopping rules allow for site-specific differences and avoid terminating the intervention in all sites if one site shows harmful effects during the interim analyses. The rules are:

if the average impact is negative, the study will pause intake for one month to allow for a discussion of options and agreement on study progressionif the average impact is positive, the threshold for roll-out to all participants will increase. To err on the side of caution, in this case, the reoffending prevalence would need to be 15 percentage points lower in the treatment group than control rather than 10 (e.g., 30% in control, 15% in treatment).

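### The six-month check contains a roll-out-for-benefit branch that, if acted on, could break the 12-month randomised comparison, and doing no formal test does not remove its error rate

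*Protocol article*

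**What the plan says.** The section on the interim analysis and 'backfire' check fixes the timing: "interim outcome analyses will be conducted roughly six months after the trial start date, defined as the date of first randomisation in any site". The stated purpose is to detect adverse effects, with harm defined as treatment prevalence at least 10 percentage points above control. On error control it says that "it will not involve statistical analysis to avoid" alpha spending.

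The section then gives "pre-specified limits or stopping rules that will inform the decision on the study continuation post the initial six-month period". One of these concerns benefit rather than harm. If the average impact is positive, "the threshold for roll-out to all participants will increase", and "the reoffending prevalence would need to be 15 percentage points lower in the treatment group than control rather than 10"; the example is 30% in control against 15% in treatment.

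Under Outcome measures, the primary outcome is "the number of violence against the person offences attributed to an individual within one year of randomisation". The section on intention-to-treat analysis uses the same window, "the number of violent offences attributed to an individual in the twelve calendar months following the randomisation", and keeps each person in the arm to which they were randomised.

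**The concern.** Three fixed elements do not fit together: a look justified by harm, a rule at that look that can lead to the programme being offered to everyone, and a primary outcome that needs 12 months in the allocated condition. In a 1:1 trial, all participants includes controls. A control who receives the programme during the 12 months still counts as a control under intention to treat, so acting on the rule would weaken the one comparison that the trial is sized to make. The protocol pooled its sites because no single site could be powered, so it has little to spare.

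The second issue is the reasoning about alpha. A threshold on the difference between arms, set in advance and linked to an action, is a decision rule. It can be crossed by chance whether or not anyone computes a p-value.

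**Working it through.** **Timing.** Longest possible follow-up at the look: about 6 months. Primary window: 12 months. Participants with a complete primary outcome at the look: 0.

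**The plan's own figures.** No operating characteristic is given for the interim rule, so there is none to reproduce. The dilution step uses the stated design: about 1,700 people, a 26% relative reduction (rate ratio 0.74), 80% power. That figure does not quite follow from Table 2. Linear interpolation between the 0.8 and 0.7 columns at n = 1,700 gives power 0.6461 + 0.6 × (1 − 0.6461) = 0.858 at 26%. The point here does not depend on the difference; both versions are used below.

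**Dilution.** Let f be the share of a control's 12-month window that falls after roll-out. Assume a constant effect that starts on exposure and the same uptake as in the treatment arm. Then

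ITT rate ratio = RR / [(1 − f) + f × RR].

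- f = 0.5: 0.74 / (0.5 + 0.37) = 0.851
- f = 0.75: 0.74 / (0.25 + 0.555) = 0.919

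The standard error implied by 26% at 80% power (two-sided 5%) is −ln(0.74) / 2.8016 = 0.3011 / 2.8016 = 0.1075. Power, if the sample stays at 1,700 and all controls share the same f:

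- f = 0.5: Φ(0.1618 / 0.1075 − 1.96) = about 32%
- f = 0.75: about 12%

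With the smaller standard error backed out of Table 2 (0.0956), power at 26% is 88% without dilution and, at f = 0.5, Φ(0.1618 / 0.0956 − 1.96) = about 39%. If roll-out were immediate at month 6, f would be 0.5 for the first person randomised and larger for everyone enrolled later. A delay in reaching controls would lower f.

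**Error rate of the 15-point boundary.** The interim sample and prevalence are not given, so both are assumptions, shown as ranges. With n per arm and prevalence p in both arms, false crossing is P(X_C − X_T ≥ 0.15n), where X_C and X_T are independent Binomial(n, p), computed exactly. The z value at 30% v 15% is 0.15 / √(2 × 0.225 × 0.775 / n). The last column is simulated (400,000 runs, p = 30%, 850 per arm at the end, final test at z > 1.96, nominal one-sided 0.025). It applies **only if crossing is itself treated as a positive result**.

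| n per arm | z at 30% v 15% | False crossing, p = 20% / 30% / 40% | Overall one-sided error if crossing counts as positive |
|---|---|---|---|
| 30 | 1.39 | 7.2% / 10.2% / 11.8% | 0.121 |
| 50 | 1.80 | 3.0% / 5.1% / 6.3% | 0.072 |
| 100 | 2.54 | 0.5% / 1.3% / 1.8% | 0.036 |
| 200 | 3.59 | 0.01% / 0.06% / 0.13% | 0.0255 |
| 400 | 5.08 | below 0.01% at all three | 0.025 |

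With a true 25% reduction from 30% (a 7.5-point gap) and 50 per arm, the boundary is crossed 19.6% of the time, and the observed gap then averages 19.9 points.

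**The case against.** Several stronger readings are tempting, and the article does not support them.

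- **That roll-out is automatic at 15 points.** The rules only inform the decision on continuation. The article does not say when roll-out would reach controls or that follow-up would end, and the full preregistered protocol, which is not shown, may say more. This stands: the damage is possible, not certain.
- **That type I error is necessarily inflated.** The primary result remains the 12-month model. With no true effect, giving controls an ineffective programme does not change their outcomes, so if recruitment and follow-up continue, the final test keeps its size. Inflation needs crossing to be treated as a positive result or to end the comparison. This stands, and the last column of the table is conditional for that reason.
- **That the interim sample is small.** Initial randomisation was of long-listed candidates in batches. If a quarter of 1,700 were in by the look (about 212 per arm, an assumption), false crossing at 30% prevalence is about 0.04%. At 10% prevalence it is 0.6% with 50 per arm and 0.03% with 100. This stands for chance crossing, but dilution does not depend on the interim sample size.
- **That the 15-point hurdle contradicts the planned effect range.** The example is a halving, while the power section considers "effects of 10%, 20%, 30% and 40% relative reductions in police-recorded violence". Those are reductions in offence counts and the interim rule uses reoffending prevalence, so the two cannot be equated. A demanding hurdle is also the declared cautious intent.
- **That the look is made with treatment labels open.** The text does not say so. Masked groups are planned for analysis, and whether that covers the interim is not stated.

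None of this answers the remaining conflict. The article itself fixes the timing, threshold, action and alpha statement, so the problem is not detail left to the statistical analysis plan.

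**Conclusion.** The concern holds in a limited form. A check described as being for harm carries a benefit branch that could lead to roll-out when nobody has a 12-month outcome. If it were acted on then, exposure of controls inside their own window would dilute the primary contrast whatever the interim sample size: from 0.74 to about 0.85 with half the window exposed, with power falling from 80% to about 32% on the plan's stated design. This rests on a constant effect, equal uptake in controls and prompt roll-out.

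The alpha sentence is not correct in general, but the practical size of the error is uncertain. It is material at about 100 per arm or fewer at the look and negligible from about 200 per arm, assuming 30% prevalence, and smaller at lower prevalence. It reaches the overall false-positive rate only if crossing is read as success or ends the comparison.

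**What to change.** Reconcile the interim section with its harm purpose and with the 12-month intention-to-treat outcome, so that the six-month check cannot break the randomised comparison. Two ways would do this statistically: limit the check to harm, or state that any roll-out leaves each control's 12-month window intact. The choice belongs to the trial team and those who agreed the rules. Separately, remove the sentence on alpha spending, or qualify it by saying what crossing the benefit threshold would and would not mean for the final inference.

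The text change is a few sentences. Because the rule belongs to an approved trial already collecting data, it also needs agreement and a dated record. The small downside is that early roll-out for benefit is given up or delayed.

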## Ethics and confidentiality

This study has been reviewed and approved by the Faculty of Arts, Cultures and Education Ethics Committee of the University of Hull (ref. 2223STAFF14) with no modifications required. The ethics application included a participant information sheet for each population group (i.e., programme participants, delivery team, stakeholders) and each research method (i.e., interview, observation, survey), a consent form for each population and method, as well as an assent form for parents or carers of those under the age of 18. It further included draft interview schedules, observation themes, survey questions, and risk assessments.

To ensure the confidentiality of all participants, data used in all publications will be anonymised and reported in aggregate, where possible. If direct quotations are used, the researchers will take necessary precautions to ensure that participants cannot be identified. There will be no direct links between the study outcomes (i.e., police-recorded offences) and qualitative data gathered for evaluation purposes.

## Data management

Data management and storage will comply with the UK Data Protection Act 2018 and YEF and University of Hull policies and procedures. To facilitate secure information transfer, we have access to encrypted CJSM accounts, and our team members have NPPV Level 2 security vetting. Data transfer, storage, and processing for summative evaluation will be done through the University of Hull’s Data Safe Haven. This system, and protocols for accessing and processing data, exceed the DSP tools standards required by NHS Digital for processing personal health data and is ISO 27001 certified, making it one of the most secure data facilities available.

## Dissemination and knowledge transfer

Our knowledge transfer strategy extends beyond the final evaluation report. Our plan ensures that our key findings, impact, and process are widely shared and accessible. This involves multiple structured outputs, collectively designed, which will distil and present our insights to diverse audiences. These will be made available in open access academic journals and showcased at global academic and stakeholder conferences, allowing us to disseminate our findings and engage in valuable dialogue with peers and stakeholders. Such discussions often lead to new insights, future collaborations, and opportunities for iterative refinement of our work.

However, given the high vulnerability of the population included in this sample, specifically in the summative evaluation, and bound by the Data Sharing Agreements signed with each of the police forces included, the authors are unable to make the data fully available without restriction. Likewise, the qualitative data gathered is confidential and might include identifiable information. The consent form specifies that all the data will be presented in a pseudonymised and unidentifiable fashion. Thus, we are unable to make the raw data public.

To promote ongoing learning and dissemination of information throughout the project’s implementation, we already incorporated various mechanisms to regularly communicate with YEF, project delivery sites, and stakeholders. Some of the current outputs include strategies for formative and summative evaluation at the programme level, theories of change at the programme level, local monitoring and evaluation plans, and system health assessments. By sharing these outputs, we aim to contribute to a broader body of knowledge, enabling other researchers and practitioners to learn from our experiences and potentially apply our insights in their contexts.

## Abbreviations

CMO: Context Mechanism Outcome
FD: Focused Deterrence
ITT: Intention To Treat
PNC: Police National Computer
RCT: Randomised Control Trial
TiDieR: Template for Intervention Description and Replication
YEF: Youth Endowment Fund
